### *Interim analyses*

Two pre-planned interim analyses were performed after the primary outcome measure was finalised for 660 and 1000 patients, respectively. Blinded interim analyses that detailed the primary outcome between treatment groups as well as information on recruitment and adverse events were presented to the Data and Safety Monitoring Board (DSMB) for their consideration. The Haybittle-Peto rule was applied (i.e. a significant p-value less than 0.001 was deemed necessary to warrant consideration of stopping the study early for benefit) (18, 19). The type I error for the final study analyses has not been adjusted to allow for interim analyses.

## **Datasets analysed**

The Consolidated Standards of Reporting Trials (CONSORT) flow diagram will be presented based on all patients who were screened for the study. All other analyses will be performed on eligible patients who underwent randomisation, i.e. the intention-to-treat population independent of compliance with the protocol. If consent is not obtained or withdrawn, data will be excluded from the analyses, unless withdrawn patients permitted the use of data up to the point of withdrawal. The primary dataset for analysis will include baseline variables, surgical data, outcomes, adverse events and protocol deviations. Following completion of the data monitoring process, data and associated data transformation code will be extracted from the study REDCap database in a Stata (StataCorp Pty Ltd, College Station, Texas) format.

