## 5.3 Consent

Consent will be sought from the parents of every child <2 years of age undergoing CPB for elective cardiac surgery over the study period. When the family is seen by the surgeons in pre-assessment clinic (usually days prior to surgery), the study will be mentioned to them by the surgeon. In addition, the study team will provide study information prior to hospitalization to families, including printed study flyers, and links to online study documentation (media release). A video detailing the study has also been prepared and is available to families. These will not replace consent, but support the consent process inasmuch as parents will have more time and more information available to

consider prior to consenting. Pre-admission contact can be made by phone, too, if not feasible directly. While parents may provide verbal consent, written consent will have to be obtained no later than the day of surgery in such circumstances.

The study team will meet the family and they will be given the study Information Statement and the consent form if they are interested. When the patient and family return to hospital for the operation, further explanation will be offered by a member of the research team and consent taken if the family wish to take part in the study. All endeavours will be made to consent parents by face-to-face meetings prior to the day of surgery, however due to the changing nature of that cardiac surgical bookings parents may be approached on the morning of surgery. Early phone contact with parents not present at the hospital or not attending pre-surgical clinics will be made. If parents give consent by phone it will be later confirmed by written consent during hospital/PICU stay.

The consent form will make it clear that standard medical treatment of children will be unaffected by participation in the study. Taking part is voluntary and will be free from coercion.

The research team will be available to field any questions from the parents prior to the consent form being signed.

The following basic principles of obtaining consent will be followed: Explain the project to the child's family in language that they understand. Generally, consent should be obtained in privacy and parents given as much time as possible to consider the study before consent.

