### ***Withdrawal of Participants***

The investigator may withdraw a patient from the study treatment and follow-up procedures if the patient:

- Is in violation of the protocol;
- Experiences a serious or intolerable adverse event
- Develops, during the course of the study, symptoms or conditions listed in the exclusion criteria
- Requires early discontinuation for any reason

The investigator will also withdraw all participants from the study treatment if the study is terminated. Patients are free to withdraw from the study at any time upon their request or the request of their legally acceptable representative. Withdrawing from the study will not affect their access to standard treatment or their relationship with the hospital and affiliated health care professionals

When a participant is withdrawn from the treatment and/or the study by the investigator, the reasons for withdrawal shall be recorded and captured in the CRF by the site research assistant. Where the participant withdraws from the treatment and/or the study themselves or is withdrawn by their parent/guardian, the site research assistant shall attempt to ascertain the reason(s) for withdrawal from the parent/legal guardian or competent participant and, where provided, record this data. Any results obtained prior to withdrawal from the treatment and/or the study will be included in the analysis, unless the participant or their parent/guardian withdraws consent to use any of the participant's data.

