## 6.2 RANDOMISATION

Study patients will be randomly allocated to NO or standard care, and stratified by age group (<42 days, 42 days -24 months) and uni-versus biventricular lesions for each site. Randomisation will be done by using REDCap randomisation. For incomplete data or withdrawal of consent the intention to treat principle will be applied.

Stratification

- age group (0 to <42 days and 42 days to 2 years)
- uni-versus biventricular
- study site

Rationale for stratification: The younger age group, including neonates (<28days) and young infants up to 6 weeks of age (<42d) represents the highest surgical risk for many procedures. The pilot study demonstrated an increased effect size in the <6 week age group. Cardiac physiology (uni- versus biventricular) is a major determinant of surgical complexity, risk, and outcome. Less than 10% of CPB procedures are performed in infants 28d to <42d, however the proportion of high-risk procedures in this age group is higher compared to older children. For this reason, we will stratify to < 6 weeks and > 6 weeks of age.

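### When a family withdraws consent and says nothing about the data, the protocol keeps the child's results and the SAP drops them; one rule should be fixed before unblinding

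*Combined protocol and SAP*

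**What the plan says.** Three places deal with a randomised child whose family withdraws.

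- Protocol 5.3, Withdrawal of Participants. Results obtained before withdrawal "will be included in the analysis, unless the participant or their parent/guardian withdraws consent to use any of the participant's data". The default is to keep.
- Protocol 6.2, Randomisation: "For incomplete data or withdrawal of consent the intention to treat principle will be applied". This points towards keeping, but says nothing about permission to use data.
- SAP, Datasets analysed: "If consent is not obtained or withdrawn, data will be excluded from the analyses, unless withdrawn patients permitted the use of data". The permission in question covers data recorded before the family withdrew. The default is to drop. The sentence just before it in the same section reads: "All other analyses will be performed on eligible patients who underwent randomisation, i.e. the intention-to-treat population independent of compliance with the protocol".

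The SAP exclusion also covers consent that was not obtained, and its exception is worded only for withdrawn patients. Protocol 5.3 gives two timings for written consent. After verbal consent, "written consent will have to be obtained no later than the day of surgery in such circumstances". Later in the same section: "If parents give consent by phone it will be later confirmed by written consent during hospital/PICU stay". The COVID-19 subsection describes verbal consent by phone and does not mention written confirmation.

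**The concern.** Membership of the primary analysis set should be settled by a single rule, fixed before anyone sees results by arm. Here the two governing documents give opposite defaults for the same family, and neither ranks them. The version history does not explain the difference. The SAP says it is based on protocol version 1.4, and the version 1.5 log entry does not mention the withdrawal rule.

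The protocol lets families withdraw at any time, so a withdrawal can come after the child's postoperative course is known. Ventilator-free days (VFD) are set to zero for a child who dies, so a few excluded children with poor courses would take away the most heavily weighted values. The imputation section covers children with missing VFD components. It does not say whether it reaches children excluded for consent reasons.

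**Working it through.** **Step 1. Where the rules differ.**

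| Situation | Protocol, Withdrawal of Participants | SAP, Datasets analysed |
|---|---|---|
| Consent withdrawn, use of data permitted | kept | kept |
| Consent withdrawn, use of data refused | out | out |
| Consent withdrawn, no wish stated | kept | out |
| Withdrawn by the investigator, or from treatment only | kept | not clearly covered; the intention-to-treat wording keeps the child |
| Consent not obtained | not addressed | out, with no exception |

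For withdrawals, the third row is the only direct conflict.

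**Step 2. The plan's sample size.** Inputs from protocol 11.2 and SAP Sample size: effect 0.2 SD, power 90%, two-sided alpha 5%, 10% withdrawals, 15% for non-normality. Per arm, n = 2 × (1.960 + 1.282)² / 0.2², which rounds up to 526.

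- 526 × 1.25 gives 658 per arm, 1,316 in total.
- 526 × 1.15 × 1.10 gives 666 per arm, 1,332 in total.
- 526 × 1.15 / 0.90 gives 673 per arm, 1,346 in total.

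The stated 1,320 is reproduced within 3% on all three routes, so the sample size is not in question.

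**Step 3. Power if children are dropped.** Treat the 15% as an efficiency loss: power = Φ(0.2 × √((n/1.15)/2) − 1.96), with n per arm.

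| Dropped | Children | n per arm | Power |
|---|---|---|---|
| 0% | 0 | 660 | 92.3% |
| 1% | 13 | 653.4 | 92.1% |
| 2% | 26 | 646.8 | 91.8% |
| 5% | 66 | 627 | 91.0% |
| 10% | 132 | 594 | 89.5% |

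**Step 4. Shift in the mean difference, under assumed losses.** The documents give no withdrawal rate by arm, so these are illustrations. If shares w1 and w0 of the two arms are dropped, and those children lie g SD below their arm's mean, the difference shifts by g·w1/(1−w1) − g·w0/(1−w0).

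- 2% against 1%, g = 1 to 2: 0.010 to 0.021 SD, or 5 to 10% of the 0.2 SD target.
- 3% against 1%, g = 1 to 2: 0.021 to 0.042 SD, or 10 to 21% of the target.
- Equal shares of equally ill children: no shift.

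**Step 5. Scale of the planned analysis.** The primary analysis is a Mann-Whitney test with median quantile regression, so the mean is only a guide. A simulation assumed 28-day death of 5% against 3%, lognormal ventilation with the pilot means of 97.8 and 65.1 hours and a coefficient of variation of 1.5, and no covariate adjustment. Every withdrawal was taken to be a silent one.

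- Withdrawal of 25% in children with VFD below 24 and 5% in the rest (about 11% overall): the Mann-Whitney probability goes from 0.606 to 0.603 and the median difference from 0.85 to 0.71 days.
- Withdrawal of 5% and 1% (about 2% overall): the median difference goes from 0.87 to 0.84 days.
- Withdrawal of 2% and 0.5%: from 0.86 to 0.85 days.

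The starting values differ slightly through simulation error. A noticeable change needs the first, extreme scenario.

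**The case against.** The strongest reply is that the conflict is narrow and its consequences are speculative. Much of this stands.

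- A reader might infer that every withdrawn child is affected. The table in the working shows otherwise: exclusion needs an active withdrawal of consent together with no stated wish about the data. A family that is merely silent after a death has not withdrawn, and its child stays in under the SAP.
- A reader might also infer that there are three rival rules. Protocol 6.2 only invokes the intention-to-treat principle and can be read with either default, so the real conflict is between two rules.
- It is tempting to say that a child consented by phone who dies before the form is signed would be dropped. No passage says that such a child counts as consent not obtained. The SAP's Randomisation section opens the module only after informed consent. Confirmation during the hospital or PICU stay can also fall on or before the day of surgery. What remains is loose wording on timing, and no statement of whether verbal consent counts.
- Exclusions would be largely visible. The CONSORT flow chart covers the consent process and the numbers randomised by arm, and consent details are listed for the supplement.
- Which default is permissible depends on the approved consent forms, which are not available here. Sites lie in three countries.

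None of this removes the opposite defaults, or supplies a rule on which document governs.

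**Conclusion.** The inconsistency is real and should be corrected. For a family that withdraws consent without stating a wish about the data, the SAP removes a randomised child whom the protocol retains, and the resulting set is not the one the SAP defines as intention-to-treat.

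The size is modest. The number of such families is unknown. The 132 children in the 10% allowance are an upper limit, and treating all of them as turning on this rule has no support in the documents. Power is barely touched, because that allowance was already budgeted.

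A reader might go further and infer that the SAP rule attenuates a true benefit. The documents do not support this. Dependence of withdrawal on outcome is possible, given that families may withdraw at any time, but it is not shown. Blinding of surgeons, anaesthetists and ICU staff makes direct dependence on arm less likely, though it does not prevent dependence through outcome. If withdrawal is unrelated to outcome, the only cost is precision. The bias figures above rest wholly on assumed withdrawal rates and are small except in the extreme case. The case for change rests on the conflicting text.

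**What to change.** Before unblinding:

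1. Replace the SAP's Datasets analysed sentence with the protocol's rule: data recorded before withdrawal are analysed unless the parent withdraws permission to use them. A VFD value already determined at withdrawal is used as observed; otherwise it is imputed as set out under Treatment of missing data. Make this subject to confirming that the approved consent form at each site allows it.
2. Reconcile the two sentences on written-consent timing in protocol 5.3, and state in the SAP whether documented verbal or phone consent counts as obtained.
3. Report, by arm, the number of randomised children excluded for consent reasons.

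The cost is a short wording change to the SAP, a clarification in protocol 5.3, and a check of the consent forms at each site.

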## **Trial profile and overview**

Recruitment of patients into the trial will be represented using a flow chart based on the CONSORT guidelines (20) (Figure 1). This will describe screened patients, those meeting exclusion criteria, eligible patients, consent process, and those randomised into each of the study arms, with the documentation of the respective primary outcome. We will report on the start and stop date of the trial and provide the recruitment graph by month including division into the contributing sites.

## **Patient baseline characteristics**

Baseline characteristics at time of randomisation will be reported for each of the two treatment groups (statistical comparison between groups will not be undertaken) (Table 1).

## **Surgical procedure and intervention characteristics**

We will provide details on the surgical procedure by treatment group, including concomitant therapies (Table 2). We will compare characteristics of the procedure that in principle may be altered by the intervention (for example, duration of CPB, duration of aortic cross-clamp) between the two study arms by presenting descriptive statistics along with estimate of difference and 95% confidence interval (CI).

We will report on the compliance with the study drug (NO) using a number of measures, reported for patients randomised to the intervention group only (Table 2). Additionally, we will list protocol deviations relating to the administration of NO in supplementary material.

## **Outcome measures analysis**

### *Primary outcome measure*

The primary outcome measure (VFDs censored at 28 days after CPB start) will be analysed using a Mann-Whitney test with differences between medians calculated by quantile regression using the simplex algorithm, inclusive of stratification variables (age group and physiology) and site included as fixed effects in the model. The effect estimate, corresponding 95% confidence interval (CI) and p-value will be presented. The unadjusted p-value using a Mann-Whitney test will also be presented (Table 3).

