### 3.3 Pre-planned secondary analyses:

- Risk adjustment for preoperative surgical risk (RACHS and Aristotle)
- Health care costs
- Subgroup analysis for age (<28d, <42d, <90d), and univentricular or biventricular hearts
- Number and duration of postoperative organ dysfunction (assessed by respiratory, cardiovascular, renal support)

- Postoperative renal failure, maximum creatinine, need and duration of renal replacement (CVVHF, CVVHDF, peritoneal dialysis, SCUF if on ECLS postoperatively), and blood, serum and urine markers of renal dysfunction including secretory/concentration capacity
- Volume and type of fluid and of transfusions given during CPB, and during the first 24 and 48 hours post CPB in PICU.
- To compare treatment response between patients depending on pre-intervention severity assessed by markers of inflammation and organ failure
- To biochemically define responders to the intervention using markers of inflammation
- Impact of open chest
- To investigate predictors of worse outcome including transcriptomic analyses, biomarkers, and clinical factors
- To investigate the association of hyperoxia with outcomes
- Subgroup analyses on infants and children undergoing several CPB procedures during first years of life, including neurocognitive and functional outcome
- Neurodevelopmental and functional follow-up
- Incidence and severity of postoperative delirium (using sedation and delirium scoring)
- Relationship of postoperative delirium and neurodevelopmental outcomes to intervention and inflammation

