### **Measured Parameters.**

**Baseline variables:** Sex, age, weight, primary cardiac diagnosis, secondary diagnoses including comorbidities (prematurity, syndrome), pre-operative disease severity (pre-operative PICU admission and length of PICU admission, ventilation and length of preoperative invasive ventilation, inotrope use and dose, prostaglandin use pre-op, diuretics, afterload reduction, infection pre-bypass). Functional assessment at baseline pre-surgery using parental interview/questionnaire to define POPC. Pre-operative medications: steroids, antibiotics, inotropes, prostaglandin, afterload reducing agents.

**Surgical intervention and bypass:** Data on performed cardiac surgical procedure, RACHS and Aristotle score (scores describing the complexity of the surgical procedure), amount and type of fluids and blood products given during surgery, length of CPB (for every run if several runs during one surgery are required), aortic cross clamp time, deep hypothermic arrest (temperature, duration), and length of NO or control delivery. Steroids given during theatre. Modified ultrafiltration. MetHb, NO.

**Postoperative status:** Data on postoperative cardiovascular status, respiratory status, urine output will be collected. Arterial and central venous (taken from jugular, subclavian, or femoral central venous catheter) blood gas analysis including lactate measurements. Laboratory tests to define organ dysfunction platelets, white cell count, haemoglobin, creatinine, base excess, pH, pCO2, pO2, SataO2, and coagulation. Amount and type of blood products given during first 24 and 48 hours. Amount of fluid given during first 24 and 48 hours. Delayed chest closure and time to chest closure. Arrhythmia (JET, etc). Intravenous steroids given during 48 hours postoperatively. Use of iNO. MetHb. Delirium. Total inotrope hours, post-operative infections, re-intubations, cardiopulmonary resuscitation, necrotising enterocolitis, readmissions to PICU and child status will be collected at 28 days. In the event that the child has been transferred to another healthcare facility, parents are asked to consider permission to access medical records within the consenting process.

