## **Sample size**

Pilot study data demonstrated a 66 hour (0.33 SD) reduction in VFDs associated with the study intervention [26]. Assuming a minimally clinically significant small effect size (0.2 SD), 90% power, two-sided alpha level of significance of 5%, 10% withdrawals, and 15% increase in sample size to account for a non-normal distribution of VFD, 1,320 patients are required (660 per group).

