#### *Subgroup and sensitivity analyses*

We will undertake two subgroup analyses that were pre-defined in the study protocol:

- age: <six weeks versus  $\geq$ six weeks; and
- physiology: univentricular versus biventricular.

Subgroup analyses will be undertaken using the same analysis methods described for the primary and secondary outcome measures, with the addition of the subgroup variable and its

related interaction term into the main regression model. For each subgroup, the relevant descriptive statistics will be presented for the primary and secondary outcomes, along with the appropriate measure of effect size (and 95% CI) and interaction effect (and 95% CI and p-value). A Forest plot will be developed to present heterogeneity between the treatment group and subgroup variable, including the p-value, and presented as a supplementary figure.

Additionally, a sensitivity analysis for study outcomes will be undertaken including the following variables: treatment group, duration of CPB, surgical complexity (recorded using the risk adjustment for congenital heart surgery [RACHS] score), blood prime using during surgery, sex and strata variables as fixed effects, and site as a random effect. Results will be presented in the same manner as primary analyses and included in the supplementary material.

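### The adjusted primary model uses only two binary strata and site; prespecifying baseline values the trial already collects is a cheap, probably modest, gain in precision

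*Combined protocol and SAP*

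**What the plan says.** **Primary analysis.** Protocol 11.1 names a Mann-Whitney test for the primary outcome. SAP "Primary outcome measure" keeps that test and adds quantile regression for the difference in medians, "inclusive of stratification variables (age group and physiology) and site included as fixed effects in the model". Age enters as below versus at or above six weeks, physiology as univentricular versus biventricular. The regression supplies the estimate, interval and adjusted p-value; the unadjusted Mann-Whitney p-value is reported beside them (SAP Table 3).

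**Baseline data.** Protocol 7.2 (Measured Parameters) lists age, weight and, under preoperative severity, "ventilation and length of preoperative invasive ventilation". SAP Table 1 reports all of these, with RACHS category. In protocol 7.2 RACHS and Aristotle are recorded with the procedure performed.

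**Risk adjustment.** Protocol 3.3 pre-plans "Risk adjustment for preoperative surgical risk (RACHS and Aristotle"). The SAP takes this up only in a sensitivity model containing "treatment group, duration of CPB, surgical complexity (recorded using the risk adjustment for congenital heart surgery [RACHS] score"), plus blood prime, sex, the strata and site. The SAP section on surgical procedure and intervention characteristics gives bypass duration as an example of something the intervention might alter. Aristotle enters no SAP model.

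**The concern.** VFD measures time off invasive ventilation, so a child's ventilation status before surgery is its closest baseline counterpart. That value is collected, yet it enters no SAP model. Weight is also unused. Age is reduced to one cut in a population running from birth to two years, so differences within each stratum are lost. The one model with RACHS also conditions on bypass duration, so it cannot serve as a clean baseline-adjusted analysis.

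The protocol itself suggests such values carry prognosis. Its background (2.1) says the severity of low cardiac output depends on the type of surgery and on the child's condition beforehand, and that perioperative death depends on procedural complexity. Death sets VFD to zero. The case mix in SAP Table 1 runs from atrial septal defect repair to Norwood, and from RACHS-1 to RACHS-6.

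At stake is the width of the interval around the main estimate, and the power of the adjusted comparison. Validity is not in question.

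**Working it through.** **Inputs** (SAP "Sample size"; same figures in protocol 11.2): "Assuming a minimally clinically significant small effect size (0.2 SD"), 90% power, "two-sided alpha level of significance of 5"%, "10% withdrawals", "15% increase in sample size to account for a non-normal distribution of VFD", 660 per group. The prognostic strength of the extra covariates is not given.

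**1. The plan's own figure.** n per arm = 2 × (1.96 + 1.2816)² / 0.2² = 525.4, so 526. The documents do not say how the two allowances combine:
- added, × 1.25: 658 per arm, 1,316 in total
- multiplied, × 1.15 × 1.10: 666 per arm, 1,332 in total
- × 1.15 / 0.90: 673 per arm, 1,346 in total

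All three lie within 2% of 1,320. The stated size reproduces, with no credit taken for covariates.

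**2. Power with no extra covariates.** Effective n per arm = 660 × 0.9 / 1.15 = 516.5. Power = Φ(0.2 × √(516.5/2) − 1.96) = Φ(3.214 − 1.96) = 89.5%.

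**3. Adding covariates, linear-model approximation.** Let R² be the assumed share of VFD variance that the extra covariates explain beyond strata and site. The standard error is multiplied by √(1 − R²). Power = Φ(3.214/√(1 − R²) − 1.96). Equivalent N = 1,320/(1 − R²).

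| Assumed added R² | Interval narrower by | Power at 0.2 SD | Equivalent N |
|---|---|---|---|
| 0 | 0% | 89.5% | 1,320 |
| 0.05 | 2.5% | 90.9% | 1,389 |
| 0.10 | 5.1% | 92.3% | 1,467 |
| 0.20 | 10.6% | 94.9% | 1,650 |

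**4. Does this carry over to median regression?** Not directly, because its precision depends on the density of the outcome near the median. As a rough check, the planned regression was simulated on invented skewed VFD data with deaths set to zero, 1,320 × 0.9 = 1,188 children and 250 replicates per setting. The ratio of standard errors, with versus without extra covariates, was 1.00 when they carried no prognosis. It was 0.97, 0.92 and 0.94 when they raised the linear R² by about 0.02, 0.08 and 0.16. Some fits stopped at the iteration limit and the data are invented, so only the direction and rough size should be read from this. The gain is modest and does not rise steadily with R².

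**The case against.** The strongest case for leaving the model alone has five parts.

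- **The named test gains nothing.** Mann-Whitney uses no covariates, so its power is unchanged. This stands. The power column above concerns only the adjusted regression, and a reader should not infer that the Mann-Whitney test is weakened by the omission.
- **The added R² is unknown.** It is tempting to say that much of the spread in VFD comes from measured preoperative condition. The documents do not support that as fact: the background statements are qualitative, and the one on preoperative condition concerns low cardiac output, not VFD. Protocol 6.2 chose the strata because they are prognostic, and protocol 5.1.2 excludes many of the sickest children, including those with chronic ventilator dependency. The gain beyond the strata could be near zero. This stands.
- **Baseline prognosis is already addressed.** A reader might infer that no planned analysis adjusts for baseline prognosis alone. That goes too far: the strata are themselves prognostic, and protocol 3.3 pre-plans risk adjustment without mentioning bypass duration. What remains true is narrower: the SAP fits RACHS only beside bypass duration, and has no model with preoperative ventilation, weight or continuous age.
- **Data quality.** Protocol 7.6 and SAP "Data monitoring" verify stratification and outcome items for every child, but cohort descriptors in a 10% sample. The proposed covariates are not named among the fully verified items. This is a real cost, though baseline error unrelated to arm would mainly reduce the gain.
- **Timing.** SAP "Interim analyses" reports both looks as already done, so a new primary model would be a late change. The SAP keeps the trial statistician blinded until its analyses are complete and provides for declared changes, so the list can still be fixed blind.

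These points limit the size and raise the cost somewhat. None makes the adjustment harmful.

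**Conclusion.** The point holds as a modest efficiency improvement. The adjusted primary analysis leaves out baseline values that the trial already collects and that plausibly bear on VFD, and the SAP gives no reason.

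The benefit is confined to the regression estimate, its interval and the adjusted p-value. For an assumed added R² of 0 to 0.20, the interval narrows by 0% to about 11%, and power at 0.2 SD moves from 89.5% to about 94.9%. Those figures rest on an R² that the documents do not supply and on a linear-model formula; median regression may gain less.

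A reader might take this as a flaw in the primary model or in the sample size. It is neither. Adjusting for stratification factors and site is valid, and the trial essentially meets its stated power without further covariates.

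**What to change.** Amend SAP "Primary outcome measure" before unblinding:

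1. Add preoperative invasive ventilation (yes/no), age as a continuous term with the age stratum kept, and weight to the quantile regression, alongside physiology and site. State the functional forms.
2. Keep the strata-and-site regression as a sensitivity analysis, and report the unadjusted Mann-Whitney p-value as planned.
3. Add RACHS to the primary regression only if it can be scored from the procedure planned before bypass. Otherwise fit it in a sensitivity model without bypass duration.
4. State how missing baseline values are handled, and put the same covariates in the imputation model, which now holds only arm, site and the strata.

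No new data collection is needed. The costs are a few more parameters with over 1,000 children, handling of rare missing baseline values, and a small change to the published code. Source checks on these covariates may cover only a 10% sample unless extended. The change must also be declared as made after the interim analyses.
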